#### In Control group

After Self-directed learning session, learning material on antimicrobial resistance, antimicrobial stewardship and infection control will be shared to all the participants and one hour will be given to them for self-study. Immediate post-test will be taken after one hour of self-study and encourage to do self-learning with provided learning material for four weeks.

---

#### STRATEGIES TO IMPROVE ADHERENCE TO INTERVENTIONS

To improve adherence to intervention protocol, text message in WhatsApp and email will be send to all the participants. The researcher will interact with participants weekly for one month on a Zoom online platform to provide guidance on self-directed learning and answer questions about learning methods. However, no lectures will be given on the learning content so that outcome variables are not affected.

To promote participant retention and minimize the risk of communication between participants in the control and experimental groups during the 4-week of follow-up period, we will implement several strategies. Participants will be instructed on maintaining confidentiality of group assignments and intervention details. The control group will be assured of getting access to the AMS game at the end of the study to reduce tendency for seeking premature information. Only experimental group will get login code for zoom platform for playing AMS game, ensuring only the assigned group can attend each session. During the game-based learning session, all participants will be asked to keep their cameras on to ensure that only the experimental group participants are present.

---

#### STRATEGIES FOR PROMOTING PARTICIPANT RETENTION AND ENSURING COMPLETE FOLLOW-UP

The researcher will follow up with participants who miss sessions or show non-compliance, offering support and solutions if needed via email, WhatsApp or phone call. Participants with workload, technological issues, or personal difficulties will be offered solutions (e.g., flexibility in gaming session or SDL discussion session, technical support). Participants who deviate but do not withdraw will be included in an intention-to-treat analysis to preserve randomization integrity. Those who fail to engage or express a desire to withdraw will be removed from the study and documented with reason of withdrawal for proper interpretation of study result and impact on sample size. If attrition is high, additional participants will be randomized to fill gaps and maintain the study's statistical power.

---

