#### **Exclusion criteria:**

1. Students who have received previous classes or training in antimicrobial resistance, antimicrobial stewardship and infection control should be excluded to prevent any potential influence on the intervention's outcomes.
2. Students who have a record of irregular attendance in class, as SDL requires dedication and regularity.
3. Students who continuously fail to engage in intervention or express a desire to withdraw can be removed from the study.

---

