#### **SAMPLE SIZE**

The study hypothesize that the self-directed learning abilities and knowledge acquisition among participants attending the game based learning would be superior to those attending the conventional learning. The sample size is determined using G\*Power (Version 3.1.9.7). Assuming a significance level of 0.05 and effect size of 0.5 (based on meta-analysis study\* which estimated a medium effect size in favor of game-based learning over learning without gamification), 64 participants per arm will be required to achieve a statistical power of 80%. Considering a dropout rate of 10%, 70 participants per arm, 140 participants in total, is required.

- Census sampling will be done to eliminate the selection bias. All the basic Bsc.Nursing students from two semester will be enrolled in study with hundred in each experimental and control group. Total 200 students is planned to be enrolled.

---

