## STATISTICAL METHODS

The study will use SPSS version 21, with tests like Shapiro-wilk, skewness, and kurtosis to evaluate the normal distribution of variables. Pre-test homogeneity will be assessed using descriptive statistics, independent t-tests, chi-square tests, and Fisher's exact test. ANOVA will compare differences in SDL ability, PL competency, and knowledge between groups. Regression analysis will explore the relationship between independent variables and dependent outcomes. Differences between pre-test and post-test will be analyzed using paired t-test. All statistical analysis will be two-sided, with a p-value less than 0.05 considered statistically significant.

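### Removing randomised students for non-engagement contradicts the promised intention-to-treat analysis and can bias the comparison, plausibly towards the game arm

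*Protocol*

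**What the plan says.** Three statements in the protocol's section on retention and complete follow-up bear on this point:

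- "Participants who deviate but do not withdraw will be included in an intention-to-treat analysis to preserve randomization integrity".
- The next sentence: "Those who fail to engage or express a desire to withdraw will be removed from the study", with the reason documented.
- "If attrition is high, additional participants will be randomized to fill gaps", so as to maintain power. No threshold for high attrition is given.

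Exclusion criteria, item 3, states the removal rule again with different force: "Students who continuously fail to engage in intervention or express a desire to withdraw can be removed from the study".

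No section defines failure to engage, names who decides, or says that removed students are still assessed at 4 and 12 weeks.

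Engagement is observed differently in the two arms. The experimental arm has four scheduled game sessions. The online sessions need a log-in code that only this arm receives, and during game sessions "all participants will be asked to keep their cameras on". The control arm has one hour of self-study followed by a test, and is then encouraged to study alone for four weeks. Weekly Zoom guidance for one month is described for participants in general. The section on blinding says that the researcher cannot be blinded.

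**The concern.** A student who stops attending but does not ask to leave has deviated without withdrawing. One sentence keeps that student in the analysis and the next removes the student from the study. Listing the rule under exclusion criteria does not make it an eligibility rule, because engagement with an intervention cannot be known before allocation.

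If removal is followed as written, the analysed groups are no longer the randomised groups. The SDLI, a primary outcome, scores learning motivation, planning and self-monitoring, and these traits are likely to be related to whether a student keeps engaging. If removal falls more heavily on one arm, that arm keeps its more engaged students and the difference between arms partly reflects selection.

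This cannot be left to an analysis plan. If removed students are not assessed, no later analysis can recover their outcomes.

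**Working it through.** **The plan's own figure.** Inputs from Sample size and Statistical methods: "Assuming a significance level of 0.05 and effect size of 0.5", power 80%, two-sided testing. A two-sample t-test (noncentral t) gives n = 63.8, so 64 per arm, as stated. The 70 per arm appears to be 64 × 1.10 = 70.4; dividing by 0.9 gives 71.1, so 72. After a 10% loss, 70 × 0.9 = 63 remain, with 79.5% power against 80.1% at 64. The point below does not depend on this difference.

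**Bias from removal.** These inputs are assumptions, because the documents give no removal share and no correlation:

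- engagement is standard normal;
- it has correlation r = 0.3 to 0.5 with the analysed outcome (change in SDLI, in SD units of that outcome);
- the least engaged share q of an arm is removed;
- the true effect is zero.

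Removal shifts that arm's mean by r × φ(z_q)/(1 − q), where z_q is the q-quantile of the standard normal.

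- q = 0.10: φ(z_q)/(1 − q) = 0.195
- q = 0.20: φ(z_q)/(1 − q) = 0.350

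The type I error is P(|Z + bias/SE| > 1.96). With removal from the game arm only, SE = √(1/(70(1 − q)) + 1/70). For q = 0.20 and r = 0.5, SE = √(1/56 + 1/70) = 0.179, bias/SE = 0.175/0.179 = 0.98, and the error is 16.4%.

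Results at 70 per arm follow (bias from unrounded multipliers). The simulated columns come from 20,000 trials per scenario and show type I error without / with replacement.

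| Removed, game / control | Bias, r = 0.3 | Simulated | Bias, r = 0.5 | Simulated |
|---|---|---|---|---|
| 10% / 0% | +0.058 SD | 6.3% / 6.8% | +0.097 SD | 8.3% / 8.8% |
| 20% / 0% | +0.105 SD | 9.5% / 9.3% | +0.175 SD | 16.9% / 18.6% |
| 20% / 10% | +0.046 SD | 5.8% / 6.0% | +0.077 SD | 7.3% / 7.6% |
| 10% / 10% | 0 | 4.8% / 4.9% | 0 | 5.0% / 4.6% |
| 0% / 10% | −0.058 SD | 6.4% / 6.6% | −0.097 SD | 9.0% / 8.9% |

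The formula gives 6.3%, 8.7%, 9.0% and 16.4% for the four game-only cases (10% then 20% removed; r = 0.3 then 0.5 in each).

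**Replacement.** The simulation refilled each arm to 70 with students subject to the same removal rule. The bias was unchanged and the numbers were restored.

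**Pool for replacements.** Sample size plans to enrol all 200 students, leaving 200 − 200 = 0. Recruitment samples 70 from each of two semesters, leaving 200 − 140 = 60. The two sections need reconciling.

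**Cost of analysing everyone.** Assume that non-attenders in the game arm gain nothing. Then d = 0.5 × (1 − q):

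| Share gaining nothing | d | Power at 70 per arm | n per arm for 80% |
|---|---|---|---|
| 0% | 0.50 | 83.6% | 64 |
| 10% | 0.45 | 75.3% | 79 |
| 20% | 0.40 | 65.2% | 100 |

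**The case against.** The strongest defence is a two-tier reading. Exclusion item 3 concerns continuous failure to engage, and the retention section speaks of documenting a reason for withdrawal. Partial deviation would then be kept under intention-to-treat, and persistent non-participation would count as withdrawal. This softens the contradiction but does not remove the problem: the boundary is undefined, and the second tier is still removed after randomisation for something other than the student's own wish to leave.

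Several stronger readings are tempting, and the documents do not support them:

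- *The bias favours the game.* No section says which arm would lose more students. Equal removal by the same process gives no net bias, and heavier removal in control reverses the sign.
- *Control engagement is unobserved.* The weekly Zoom contact is not restricted to one arm, follow-up of missed sessions covers the self-directed learning discussions too, and controls have a supervised first hour and test. Control engagement is less visible, not invisible.
- *A false superiority result will follow.* In the game-only cases the type I error is about 6-16%, so roughly 84-94% of null trials would still be non-significant.
- *Removed students are always replaced, and nobody is left to replace them.* Replacement is conditional on high attrition, and the pool is empty only if all 200 are enrolled.
- *The 10% allowance already covers the losses.* It leaves 63 per arm against the required 64.

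A further limit stands. The protocol describes the SDLI result as a pre-post difference, and stable differences in motivation partly cancel in a change score. If engagement is more weakly related to change than assumed, the bias is smaller.

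**Conclusion.** The point holds as a conflict in the text with a possible bias. The protocol removes randomised students for a post-randomisation event, against its own intention-to-treat statement, and replacement does not repair the comparison. Because non-attendance is more visible in the game arm and the researcher is unblinded, the bias plausibly favours the game, but that direction is an inference.

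The size rests wholly on assumed removal shares and on a correlation of 0.3-0.5 with change in SDLI. The game-only cases, at 0.06-0.18 SD, amount to about 12-35% of the planned "effect size of 0.5" and are the extreme split. With 20% against 10% removed, the bias is about 0.05-0.08 SD. The contradiction needs correcting before enrolment whatever values turn out to apply.

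**What to change.** 1. Delete exclusion item 3 and the removal of students for non-engagement in the retention section.
2. State that every randomised student is followed to week 12 and analysed in the assigned arm, whatever the attendance.
3. Separate stopping the intervention from withdrawing consent. Data collection stops only on withdrawal of consent, and data already collected are kept.
4. Delete the replacement rule.
5. Report attendance by arm descriptively.

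The edits are to wording, but they have a statistical cost. Non-attenders dilute the effect, so the stated 80% power should be read or restated accordingly: about 75% to 65% at 70 per arm if 10-20% of the game arm gains nothing, with 79 to 100 per arm needed for 80%. The diluted estimate is the effect of assigning students to the game, which is what an intention-to-treat analysis estimates.

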## OUTCOMES

The outcome measurements will be conducted at baseline, immediately postintervention, 4 weeks postintervention, and 12 weeks postintervention using the same data collection tool.

### **Primary Outcome:**

#### **1. Self-Directed Learning abilities Improvement:**

The primary outcome would be improvement in self-directed learning (SDL) abilities among nursing undergraduates after intervention. This will be measured by using validated SDLI tool, which assess key SDL competencies such as:

- a. Learning motivation
- b. Planning and implementing
- c. Self-monitoring and
- d. Interpersonal communication

The difference in Pre- and Post- intervention SDLI scores between the experimental and control groups would highlight the effectiveness of game-based learning in improving SDL abilities.

#### **2. Knowledge Acquisition**

Another primary outcome is improvement in knowledge acquisition in the topic antimicrobial resistance, antimicrobial stewardship & infection control. This will be assessed by using structured questionnaire developed and validated by researcher. The difference in scores between the game-based learning and conventional SDL group would highlight the effectiveness of each strategy in improving knowledge acquisition and retention.

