#### OBJECTIVES

1. To assess the effect of game-based learning as an innovative self-directed learning strategy on knowledge acquisition among nursing undergraduates.
2. To assess the effect of conventional learning method on knowledge acquisition among nursing undergraduates.
3. To evaluate the effect of game-based learning as an innovative self-directed learning strategy on self-directed learning abilities among nursing undergraduates.

4. To evaluate the effect of conventional learning method on self-directed learning abilities among nursing undergraduates.
5. To compare the impact of game-based learning and conventional learning method on knowledge acquisition among nursing undergraduates after 12 weeks of intervention.
6. To determine whether game-based learning is superior to conventional learning in improving self-directed learning abilities in nursing undergraduates after 12 weeks of intervention.

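### Two primary outcomes are each tested at an unadjusted 0.05 with no rule on whether one or both must succeed, and the sample size covers one test only

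*Protocol*

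**What the plan says.** The Outcomes section of the protocol lists two items under Primary Outcome. The first is SDLI: "The primary outcome would be improvement in self-directed learning (SDL) abilities among nursing undergraduates after intervention". The second is knowledge: "Another primary outcome is improvement in knowledge acquisition in the topic antimicrobial resistance, antimicrobial stewardship & infection control". The Hypothesis section gives each its own directional hypothesis, H1 for self-directed learning ability and H2 for knowledge score.

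Statistical Methods sets one threshold for everything: "All statistical analysis will be two-sided, with a p-value less than 0.05 considered statistically significant". It gives no order of testing, no adjustment and no success rule.

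The Sample Size section introduces its calculation with both outcomes: "The study hypothesize that the self-directed learning abilities and knowledge acquisition among participants attending the game based learning would be superior". It then makes a single calculation: significance level 0.05, effect size 0.5, 80% power, 64 per arm, raised to 70 per arm (140 in total) for 10% dropout. The same section also plans to enrol 200, with 100 in each group.

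On timing, objectives 5 and 6 place both between-group comparisons at 12 weeks (for SDLI: "To determine whether game-based learning is superior to conventional learning in improving self-directed learning abilities in nursing undergraduates after 12 weeks of intervention"). The outcome definition for SDLI refers only to "The difference in Pre- and Post- intervention SDLI scores between the experimental and control groups". The definition for knowledge and the Statistical Methods section name no visit either.

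**The concern.** With two primary outcomes, the claim that game-based learning is superior needs a rule: one win is enough, or both are required. The rule decides which operating characteristic changes. If one win is enough, there are two chances of a false positive, each at 0.05. If both are required, the chance of success is the chance of two wins together, which is lower than the 80% for one.

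The protocol's wording points both ways. The sample-size hypothesis joins the outcomes with a conjunction, while H1 and H2 separate them. If the results split, with one outcome significant and the other not, the protocol does not say whether the trial succeeded, and the choice could be made after the data are seen.

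**Working it through.** **Inputs.** From Sample Size: alpha 0.05, standardised effect d = 0.5, 64 per arm, 10% dropout, and a planned enrolment of 200. From Statistical Methods: two-sided tests. From Study Design: 1:1 allocation. The protocol gives no correlation between SDLI and knowledge, so a range of 0 to 0.7 is assumed. The same d = 0.5 is used for both outcomes because it is the only effect size the protocol offers.

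**1. The protocol's own figure.** A two-sample, two-sided t-test at 0.05 with d = 0.5 and 80% power needs n = 63.8, so 64 per arm, with power 80.1%. As a hand check, the noncentrality is 0.5 × √(64/2) = 2.83, and the normal approximation gives Φ(2.83 − 1.96) = Φ(0.87) ≈ 81%. The stated figure is reproduced for one test. (Allowing for dropout, 64/0.90 = 71.1, so 72 rather than 70. The gap is too small to matter here.)

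**2. Rule A, either outcome suffices.** With independent test statistics, familywise error = 1 − (1 − 0.05)² = 1 − 0.9025 = 9.75%. With correlation r it is 1 − P(|Z₁| ≤ 1.96 and |Z₂| ≤ 1.96) under a bivariate normal. The chance of at least one win when both effects are real is 2 × 0.80 − P(both win).

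**3. Rule B, both outcomes required.** With 80% power for each and independence, P(both win) = 0.80² = 64%. With correlation it is the matching bivariate normal probability. Familywise error stays at or below 5%, because both tests must pass at 0.05.

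| Assumed correlation | Rule A: familywise error | Rule A: chance of at least one win | Rule B: power for both |
|---|---|---|---|
| 0 | 9.75% | 96% | 64% |
| 0.3 | 9.5% | 93% | 67% |
| 0.5 | 9.1% | 91% | 69% |
| 0.7 | 8.3% | 89% | 71% |

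**4. If 200 are enrolled.** 100 per arm less 10% leaves 90 per arm. Power for one test is then 91.6%, and for both, if independent, 0.9156² = 83.8%. Positive correlation raises it. Familywise error under Rule A does not change with n.

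**5. Cost of keeping two equal primaries.** Splitting alpha (0.025 each) leaves 71% power per outcome at 64 per arm. Restoring 80% needs 78 per arm, and 78/0.90 = 86.7, so 87 per arm (174 in total). Requiring both, with 80% joint power under independence, needs 84 per arm, and 84/0.90 = 93.3, so 94 per arm (188 in total).

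**The case against.** The protocol never promises a 5% familywise rate. It states a significance level and a per-test threshold. H1 and H2 concern different constructs, and each taken alone is tested at 5% with about 80% power. That is correct per hypothesis, and it would be enough if the two claims were reported as unrelated questions. But the protocol calls both outcomes primary, sizes the trial under one joint superiority hypothesis, and never says how a split result is read.

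Multiplicity detail is often left to a statistical analysis plan, and one may exist. That argument would carry more weight if the protocol were silent. It is not: it fixes 0.05 for all analyses and states a power that belongs to a single test.

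The planned enrolment of 200 would lift joint power above 80%. This stands as a qualification. However, the same section says that 140 are required, and Recruitment selects 70 from each of two semesters, which is also 140. The stated power rests on 64 per arm.

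A reader might infer six primary tests, since both outcomes are measured at three follow-ups: "The outcome measurements will be conducted at baseline, immediately postintervention, 4 weeks postintervention, and 12 weeks postintervention using the same data collection tool". The documents do not support this. That sentence is a measurement schedule, and objectives 5 and 6 put both between-group comparisons at 12 weeks (for knowledge: "To compare the impact of game-based learning and conventional learning method on knowledge acquisition among nursing undergraduates after 12 weeks of intervention"). The defensible count is two. What remains is a gap in clarity, because the outcome and statistics sections do not repeat the visit.

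Ranking SDLI above knowledge is also a choice, since the aim and H2 include knowledge. It is nevertheless the choice closest to the text: the research question and H1 concern self-directed learning ability, and objective 6 is worded as a test of superiority.

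**Conclusion.** The concern holds for two tests at 12 weeks with no success rule. Which figure fails depends on the rule the protocol leaves out. Under an either-outcome rule, familywise error is about 8.3% to 9.75% instead of 5%. Under a both-outcomes rule, power at 64 evaluable per arm is about 64% to 71% instead of 80%.

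It would be tempting to say that the trial loses both its error rate and its power. No single reading gives that. Where error is inflated, the chance of at least one win is 89% to 96%. Where power falls short, error is controlled.

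The ranges rest on assumed correlations of 0 to 0.7 and on d = 0.5 for both outcomes. The power shortfall also rests on the 64-per-arm basis and disappears (about 84% or more) if 200 are enrolled and 90 per arm complete. The error inflation does not depend on n. The point goes beyond missing detail, because it settles what the trial may conclude when the two outcomes disagree.

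**What to change.** Before any outcome data are examined:

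- **Outcomes (both primary entries) and Statistical Methods:** make the between-group comparison of SDLI total score at the 12-week visit the single primary endpoint. Test knowledge at 12 weeks second, two-sided at 0.05, only if SDLI is significant. Name the 12-week visit in each place so that it matches objectives 5 and 6.
- **Immediate and 4-week results:** report them as estimates with confidence intervals, without superiority claims.
- **Sample Size:** state that the 80% power applies to the first test only, and reconcile the 140 required with the 200 planned.

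The fixed sequence holds familywise error at 5% with no alpha split and no extra students, so the cost is wording. There are two downsides. Knowledge cannot be claimed confirmatorily if SDLI fails. The chance of claiming both outcomes also stays at about 64% to 71% with 64 per arm. If the sponsor prefers two equal primaries, the protocol should state the rule and use the larger sample sizes in step 5 of the working.
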